## Data collection and management

### Data management

Data (soft-copy) will be kept in a password protected database “SingHealth REDCap”. All documented (hard copy) data including consent forms, data collection forms and neurocognitive, functional and ADL assessment forms will be stored in a secured research folder. Research coordinators will help ensure per-protocol follow-up and filling-in of data targets. 3-monthly random checks on the data will be performed by the investigators to ensure integrity and quality.

## Statistical methods

### Statistical analysis plans

Efficacy analyses will be performed using the intention-to-treat principle. Per-protocol analyses may be performed as secondary analyses. Safety analyses will include all patients who started treatment and will be performed according to the actual treatment received.

The primary endpoint, time to target lesion progression, will be defined as the time from randomisation to target lesion progression. Patients who pass away before documented target lesion progression will be censored at the last brain imaging assessment. Time to target lesion progression will be compared between the 2 treatment groups using a 2-sided log-rank test.

Time to intracranial progression, time to symptomatic brain progression, progression-free survival and overall survival will be defined as the time from randomisation to intracranial progression, symptomatic brain progression, overall progression and death from any cause respectively. All time-to-event endpoints will be summarized using the Kaplan-Meier method. Treatment arms will be compared using log-rank tests and Cox proportional hazards models, adjusting for the stratification variable (number of brain metastases). Other prognostic variables such as histology, ECOG status and disease-specific GPA class may also be included in the Cox models.

Adverse events will be recorded according to CTCAE version 5.0 and summarised by treatment arm.

Cognitive test (HVLT-R and CTT) scores will be standardised based on published norms: (Patient value – Published-norm mean value) ÷ Published-norm standard deviation value. Cognitive deterioration will be defined as a decline of at least 1 SD in score from baseline. FACT-BR scores will be transformed to a 0- to 100- point scale. A 10-point decrease will be considered clinically significant. Deterioration in functional independence will be defined as a decline of at least 10% in the Barthel ADL index from baseline.

The proportions of patients with cognitive deterioration, QoL deterioration and functional independence deterioration will be compared between treatment arms using Fisher’s exact test. A sensitivity analysis will be conducted assuming patients who had not completed the neurocognitive assessment or had passed away prior to the assessment time-point, had cognitive deterioration. Change from baseline values will be compared using 2-sample t-tests and repeated measures linear regression, adjusting for the stratification variable (number of brain metastases).

All analyses will use a 2-sided 0.05 level of significance. There will be no adjustment for multiple comparisons.

There is no planned interim analysis for this study.

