## Introduction

### Background

The management of brain metastases presents a significant challenge in oncology. Whole brain radiation therapy (WBRT) is widely given to improve neurological symptoms, stop brain metastasis progression and possibly prolong survival. Unfortunately, neurocognitive functional decline is reported in a significant number of patients who undergo WBRT at rates of 31–57% at 3 months and 48–89% at 1 year [1].

The hippocampus plays a key role in learning, memory and cognitive function [2–4]. The significance of hippocampi radiation in clinical studies is emerging. Gondi et al. showed that a dose of > 7.3Gy to at least 40% of the hippocampus resulted in a significant decline in delayed recall in adult brain cancer patients [5].

A recent phase 3 trial, NRG-CC001, randomised 518 patients to Hippocampal avoidance-WBRT (HA-WBRT) against standard WBRT. Cognitive endpoints were measured using a test battery of Hopkins Verbal Learning Test-Revised (HVLT-R), Controlled Oral Word Association, and Trail Making Test (TMT) Part A & B. At a median follow-up for alive patients of 7.9 months, a significant reduction in cognitive failure risk was noted (HR, 0.76; *P* = 0.03) in the HA-WBRT arm. This difference was most significant in the 4-month TMT Part B scores and the 6-month HVLT-R score. The median overall survival (OS) and progression free survival (PFS) did not differ and there was no increase in hippocampal relapses. However notably, OS and PFS in the HA-WBRT arm were poor at 6.3 months and 5.0 months respectively [6].

This trial introduced HA-WBRT as a new standard option in patients with multiple brain metastases and good prognosis. However, some clinicians would still favour the use of Stereotactic Radiosurgery (SRS) over HA-WBRT in patients with low volume brain metastases. The reasons could possibly be better cognitive sparing or tumoral control due to the higher ablative doses used in SRS. Several trials are underway comparing the use of HA-WBRT against SRS (ClinicalTrials.gov identifier: NCT03550391, NCT03075072 and NCT04277403).

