#### Secondary endpoints

Intracranial Progression▪ Target lesion or distal brain lesion▪ Symptomatic or asymptomatic brain lesion
PFSOS▪ Neurological or non-neurological death▪ Cancer or non-cancer related deathCognitive Function▪ HVLT-R (immediate recall, delayed recall, and total recall)▪ Colour Trail Test (CTT) – a language-free version of the TMTQuality of Life (QoL)▪ Functional Assessment of Cancer Therapy with Brain Subscale (FACT-BR)▪ Euro QOL – 5 Dimension – 5 Level (EQ-5D-5L)Activities of Daily Living (ADL)▪ Barthel Index of ADLsToxicity▪ Scored using Common Terminology Criteria for Adverse Events (CTCAE) ver5.0 criteria▪ Presence of radiation necrosis (asymptomatic or symptomatic)

All time points will be taken from the time of randomisation to event. If response assessment of the target lesion(s) is uncertain or equivocal, this should be reassessed by a multi-disciplinary team for clarification. When needed, this may be followed up with advanced imaging or histology.

Cognitive function, ADL and QoL will be assessed using patient-directed questionnaires that have been validated, available in local languages and used in the trials mentioned earlier for ease of comparison. These tests are optional but encouraged for all patients and will be conducted by a trained physician or clinical research associate at specified time points (Table 3). The total duration of the combined test is estimated to be 30 min. In the analysis of cognitive function, ADL and QoL, each patient will serve as his/her own control. The test results at each follow-up (post-treatment) time point will be compared to the baseline (pre-treatment) test result.

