### Sample size

Assuming a 6-month target lesion control rate of 50% in the HA-WBRT arm, we will need 60 subjects (30 per arm) to detect a hazard ratio of 0.27 [9] between the 2 arms with 80% power using a 2-sided log-rank test at 5% significance level. A hazard ratio of 0.27 means the 6-month target lesion control rate in the HA-SIB-WBRT arm is expected to be 83%. These calculations assume that subjects will be followed up till target lesion progression, or for a minimum of 6 months. Assuming a 40% non-evaluable rate, an estimated total sample size of 100 subjects will be required.

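### With deaths censored, Kaplan-Meier will not give the proportion of patients whose target lesions progress; the progression endpoints need cumulative incidence with death as a competing event

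*Protocol article*

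**What the plan says.** Under Statistical analysis plans, the protocol defines the primary endpoint as the time from randomisation to target lesion progression and compares the arms with a two-sided log-rank test. On death it says: "Patients who pass away before documented target lesion progression will be censored at the last brain imaging assessment". On presentation it says: "All time-to-event endpoints will be summarized using the Kaplan-Meier method". That covers time to intracranial progression and time to symptomatic brain progression as well. The section names no competing-risk method.

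The Sample size section expresses the treatment effect as 6-month control rates: "Assuming a 6-month target lesion control rate of 50% in the HA-WBRT arm", with a hazard ratio of 0.27, so that "the 6-month target lesion control rate in the HA-SIB-WBRT arm is expected to be 83"%.

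On mortality, the Background reports for an earlier phase 3 trial that "OS and PFS in the HA-WBRT arm were poor at 6.3 months and 5.0 months respectively". For this trial the eligibility criteria require a life expectancy of at least 6 months; no median survival is given. Deaths are classified under overall survival in the secondary endpoints as "Neurological or non-neurological death".

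**The concern.** A patient who has died can no longer have target lesion progression. Censoring treats that patient as someone who could still progress later, at the same rate as those who remain under observation. The resulting curve answers what control would be if nobody died first. Readers usually take a 6-month control rate as the proportion of patients in whom the treated lesions held or failed, and where deaths are frequent the two quantities differ.

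The difference is larger in the arm with more progression, so the absolute benefit between arms is inflated as well as the individual rates. The design states its effect in exactly these terms (50% against 83%), so this is how the result is likely to be read.

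A second issue is separate. Censoring is at the last scan and not at death. A patient whose lesion progresses and who dies before the next scan is counted as controlled up to the earlier scan. The Discussion expects better intracranial control to reduce neurological death, so by the protocol's own rationale progression and death are linked, and independence cannot be taken for granted.

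**Working it through.** **The plan's own figures.** Inputs from Sample size: 50% control at 6 months, hazard ratio 0.27, 30 patients per arm, 40% non-evaluable.
- 0.5^0.27 = 0.829, which agrees with the stated 83%.
- A simulated log-rank test with exponential times, 30 per arm, 6 months of follow-up and no deaths has power 0.804, which agrees with "with 80% power using a 2-sided log-rank test at 5% significance level".
- 60 / (1 - 0.40) = 100.

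The design figures reproduce.

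**1-KM against cumulative incidence.** Monthly progression hazards:
- control: l = ln 2 / 6 = 0.1155
- experimental: l = 0.27 × 0.1155 = 0.0312

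The death hazard is d = ln 2 / (median survival). The median is an assumption. The range runs from 6.3 months (the earlier trial's HA-WBRT arm) to 18 months, with exponential times, death independent of progression and the same in both arms.
- 1-KM(T) = 1 - exp(-lT)
- Cumulative incidence(T) = l/(l+d) × [1 - exp(-(l+d)T)]

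Worked case, control arm, T = 6, median 6.3 months: d = 0.1100 and l + d = 0.2255, so 0.1155/0.2255 × [1 - exp(-1.353)] = 0.512 × 0.742 = 38.0%.

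At 6 months, 1-KM is 50.0% (control) and 17.1% (experimental), a difference of 32.9 points.

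| Assumed median survival | Dead by 6 months | Cumulative incidence, control | Experimental | Difference |
|---|---|---|---|---|
| 6.3 months | 48% | 38.0% | 12.6% | 25.4 |
| 9 months | 37% | 41.1% | 13.8% | 27.3 |
| 12 months | 29% | 43.1% | 14.5% | 28.6 |
| 18 months | 21% | 45.2% | 15.3% | 29.9 |

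At 12 months, 1-KM is 75.0% and 31.2% (43.8 points). Cumulative incidence is:
- median 6.3 months: 47.8% and 18.0% (29.8 points)
- median 12 months: 58.3% and 23.0% (35.3 points)
- median 18 months: 63.2% and 25.4% (37.8 points)

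**Progressions never imaged.** Further assumptions: scans at 1, 3, 6 and 12 months (the visits named in the Table 3 footnote; the table itself is not shown) and a death hazard of 0.08 per month before progression. In the control arm, by simulation:
- post-progression median of 3 months: about 22% of progressions before month 6 are never imaged, and Kaplan-Meier shows 55% control at 6 months where the net rate is 50%
- post-progression median of 6 months: about 12% are missed, and Kaplan-Meier shows 51%

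This bias has a different target and the opposite direction. Against actual incidence, Kaplan-Meier makes control look too low; against the net rate, missed progressions make it look too high. The two should not be added or assumed to cancel.

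**The primary test.** Simulated type I error of the log-rank test, with median survival 6.3 months and 30 per arm:
- death independent of progression: 0.050-0.055, including a death hazard ratio of 0.7 between arms
- death dependent on progression (Clayton model, Kendall's tau 1/3), equal between arms: 0.050-0.051
- death dependent and different between arms: at most 0.061

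Power under the same death models, if all 100 patients contribute, is 0.83-0.90 with 6 months of follow-up and 0.94-0.96 with 12 months.

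**The case against.** The strongest reply is that nothing here is wrong for the comparison the trial makes. Censoring deaths gives a cause-specific log-rank test, which is a proper comparison of progression rates. For a treatment aimed at individual lesions, the net rate of local control is a legitimate quantity, and Kaplan-Meier estimates it correctly when death is independent of progression. This stands: the rates are not wrong in themselves, but they are not the proportion of patients who progress.

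Four stronger readings are tempting, and the documents do not support them.
- A reader might infer that patients in this trial will die at a median of about 6 months. That figure comes from another trial's arm. This trial requires a life expectancy of at least 6 months and excludes extensive extracranial disease not controlled by systemic treatment. Only a range can be shown.
- A reader might infer that the primary test or the sample size fails. The simulated type I error and the reproduced sample size say otherwise.
- A reader might infer that informative censoring is established. The protocol's rationale makes it plausible, but its size depends on post-progression survival and scan timing, which are assumed here.
- A reader might infer that a difference in neurological death would be hidden. Cause of death is recorded under overall survival, and the arms are compared on overall survival; neurological death is only outside the primary endpoint.

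It is also fair to say that extra sensitivity analyses are often left to a fuller analysis plan, so their absence from this article is not the defect. The point rests on the censoring rule and the estimator, both of which the article states.

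**Conclusion.** The point holds for estimation and presentation, not for the primary test. As planned, 1-KM would exceed the actual proportion with target lesion progression at 6 months by about 5 to 12 points in the control arm and about 2 to 4.5 points in the experimental arm. The absolute difference would read 33 points where about 25 to 30 apply. At 12 months it would read about 44 points where about 30 to 38 apply. These figures rest on the design's own 50% and 0.27, exponential times, independent death, and an assumed median survival of 6.3 to 18 months. The direction is the same across that whole range.

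Bias from progressions that are never imaged is a separate risk. It is between about 1 and 5 points of control in the two control-arm scenarios tried, and the documents do not settle its size. The same reporting issue applies to intracranial and symptomatic progression, but it was not quantified for them.

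**What to change.** - Keep the log-rank test and the Cox model, and describe them as the cause-specific comparison.
- Report target lesion, intracranial and symptomatic brain progression by arm with the cumulative incidence function, treating death without that progression as a competing event. Kaplan-Meier curves may be shown alongside for comparison with earlier trials, labelled as net rates.
- Add a sensitivity analysis of the primary endpoint that counts death without documented progression as an event, once for neurological deaths only and once for any death. The protocol already plans the parallel analysis for cognition, where patients who died before the assessment are counted as deteriorated.

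The cost is revised analysis wording and a few more outputs. Dates and causes of death are already collected, and neither the primary test nor the sample size changes. The drawback is that the 6-month cumulative incidence figures will not be directly comparable with published Kaplan-Meier rates, which is the reason to show both.

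### The secondary endpoint labelled progression-free survival is defined without death as an event, so it is time to progression and will read longer than true PFS if any patient dies without documented progression

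*Protocol article*

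**What the plan says.** Under Secondary endpoints, PFS is listed by name only, with the general rule "All time points will be taken from the time of randomisation to event". The definition is in the Statistical analysis plans section. The sentence opens "Time to intracranial progression, time to symptomatic brain progression, progression-free survival and overall survival will be defined as the time from randomisation to", and the matching events are those in "randomisation to intracranial progression, symptomatic brain progression, overall progression and death from any cause respectively". The closing adverb makes the pairing one to one:

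- time to intracranial progression: intracranial progression
- time to symptomatic brain progression: symptomatic brain progression
- progression-free survival: overall progression
- overall survival: death from any cause

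The same section says "All time-to-event endpoints will be summarized using the Kaplan-Meier method". It gives one rule for deaths in a progression endpoint, and that rule belongs to the primary endpoint: "Patients who pass away before documented target lesion progression will be censored at the last brain imaging assessment". No rule for deaths is given for PFS, and nowhere does the article add death to the PFS event.

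**The concern.** PFS ordinarily ends at progression or death, whichever comes first. Here a patient who dies with no documented progression has no PFS event. The label and the event therefore conflict, and an analyst who follows the text will compute time to progression and report it as PFS.

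This is not a detail left to a fuller document. The article fixes a definition, and the definition does not match the name. The same sentence uses a 'time to' name for the two brain-progression endpoints, so that form of label was available.

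Death before documented progression is plausible in this population. The Background reports of an earlier randomised trial that "OS and PFS in the HA-WBRT arm were poor at 6.3 months and 5.0 months respectively". The footnote to Table 3 refers to follow-up visits at months 1, 3, 6 and 12, with windows of up to one month either way and individual deviations allowed, so a patient can die between scans. At stake is whether a reader who sees a PFS median from this trial is seeing what the name promises.

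**Working it through.** **1. What the plan's own figures depend on.** The only design calculation is in Sample size, and it concerns target lesion control. It begins "Assuming a 6-month target lesion control rate of 50% in the HA-WBRT arm" and uses a hazard ratio of 0.27. The implied rate in the experimental arm is 0.5^0.27 = 0.829, which matches the stated 83%. The inflation is 60 / (1 − 0.40) = 100, also as stated. Neither figure uses PFS, so a change in its definition leaves both as they are.

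**2. Direction.** Let T be the time to first progression or death, which is true PFS. Under the written definition a death without progression is never an event. Whether such deaths are censored or handled as competing events, the estimated progression-free proportion is at or above the true PFS proportion at every time. The two are equal only if nobody dies without documented progression.

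**3. Size, as an illustration.** Inputs:

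- True median PFS of 5.0 months. This is an assumption, scaled to the figure cited in the Background.
- Constant hazards, with deaths censored when they occur. Both are assumptions.
- q, the share of first PFS events that are deaths without progression. The article does not give it, so a range is shown.

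Formulas:

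- total hazard λ = ln 2 / 5.0 = 0.1386 per month
- hazard seen when deaths are censored = λ(1 − q)
- reported median = ln 2 / [λ(1 − q)] = 5.0 / (1 − q)
- reported proportion at t months = exp[−λ(1 − q)t]
- if death is instead a competing event, proportion without recorded progression at t = 1 − (1 − q)[1 − exp(−λt)]

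| q | λ(1 − q) | Median, months | 6 months, deaths censored | 12 months, deaths censored | 12 months, death competing |
|---|---|---|---|---|---|
| 0% (true PFS) | 0.1386 | 5.0 | 43.5% | 18.9% | 18.9% |
| 10% | 0.1248 | 5.6 | 47.3% | 22.4% | 27.1% |
| 20% | 0.1109 | 6.3 | 51.4% | 26.4% | 35.2% |
| 30% | 0.0970 | 7.1 | 55.9% | 31.2% | 43.3% |
| 40% | 0.0832 | 8.3 | 60.7% | 36.9% | 51.4% |
| 50% | 0.0693 | 10.0 | 66.0% | 43.5% | 59.5% |

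One row in full, q = 30%: 0.1386 × 0.70 = 0.0970; median 5.0 / 0.70 = 7.1 months; at 6 months exp(−0.0970 × 6) = 55.9%.

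The last column shows that the direction does not depend on the censoring assumption. The size does.

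**The case against.** The strongest reply is that this is a slip of wording in an unpowered secondary endpoint. Investigators know what PFS means, and overall progression may have been meant to include death. Nothing in the article supports that reading: the same sentence names death separately, as the event for a different endpoint. If death was intended, the text still needs correcting. The point about rank stands: the primary endpoint has its own definition and its own rule for deaths, so this does not threaten the main result.

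A reader might also infer more than the article supports:

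- *That the plan states deaths are censored for PFS.* It does not. That rule is written for target lesion progression only; for PFS it is an inference from the use of Kaplan-Meier.
- *That deaths, including treatment-related ones, are hidden.* They are absent from one curve only. Overall survival counts every death, Secondary endpoints classifies deaths as neurological or not and cancer-related or not, and the Safety section requires review of serious adverse events of grade 3 or above.
- *That the result could not be set against the 5.0-month benchmark, and that the fix would restore comparability.* The Background calls that figure PFS, but the Discussion calls it intracranial PFS. If the Discussion is right, neither the written endpoint nor a corrected overall PFS matches it directly. The article also does not say whether the figure counts deaths, and the Statistical analysis plans section plans no comparison with it.
- *That deaths without progression will be common.* The 6.3-month median survival comes from another trial. Table 1 here requires a life expectancy of at least 6 months and excludes extensive uncontrolled extracranial disease. This does not show that such deaths will be rare; their frequency is unknown.

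**Conclusion.** The point holds as an error in the definition of a secondary endpoint. As written, the endpoint is time to progression under a PFS label, and it overstates PFS whenever a patient dies without documented progression.

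The amount cannot be fixed from the article. A reported median anywhere from about 5.6 to 10.0 months against a true 5.0 rests on three assumptions: exponential times, censoring at death, and a share of 10% to 50% of events being deaths without progression. At the low end the shift is modest.

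The effect on the comparison between arms could go either way, because it depends on how such deaths divide between the arms. A claim that the definition favours one arm would not be supported. This should be fixed, but the primary conclusion does not depend on it.

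**What to change.** Amend the sentence in Statistical analysis plans in one of two ways.

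- **Preferred, if PFS is the quantity wanted:** define it as the time from randomisation to the first of overall progression (intracranial or extracranial) or death from any cause. Censor patients who are alive without progression at their last disease assessment.
- **If the quantity as written is wanted:** rename it time to progression and analyse death as a competing event, using cumulative incidence in place of Kaplan-Meier for this endpoint.

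Under Assignment of interventions, patients and treating radiation oncologists are not blinded, so the change should be made and dated before outcome data are analysed. The cost is one sentence. Under the first option reported PFS will be shorter; the sample size and primary analysis do not change.

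### As written, the 1-SD cognitive deterioration rule points the wrong way for the Colour Trail Test if that test is analysed as completion time

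*Protocol article*

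**What the plan says.** The Statistical analysis plans section of the protocol article treats the two cognitive tests together: "Cognitive test (HVLT-R and CTT) scores will be standardised based on published norms". The formula, after its opening bracket, reads "Patient value – Published-norm mean value) ÷ Published-norm standard deviation value". The next sentence gives the event definition: "Cognitive deterioration will be defined as a decline of at least 1 SD in score from baseline". Neither sentence distinguishes HVLT-R from CTT or mentions a change of sign.

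The event feeds a between-arm test: "The proportions of patients with cognitive deterioration, QoL deterioration and functional independence deterioration will be compared between treatment arms using Fisher’s exact test". Patients who died before the assessment or did not complete it are counted as deteriorated in a sensitivity analysis. Separately, "Change from baseline values will be compared using 2-sample t-tests and repeated measures linear regression", with adjustment for the stratification variable.

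The Secondary endpoints section describes the CTT only as a form of the Trail Making Test (TMT) that does not depend on language. It gives no unit, scoring direction or norm metric. It also says that the cognitive, ADL and quality-of-life tests are optional.

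**The concern.** A rule that calls a fall in score a deterioration works only when a higher score is better. That suits a recall score such as HVLT-R. It does not suit a timed test, where a patient who gets worse takes longer and the value rises. The stated formula carries the raw direction straight into the z-score, so a slower patient moves up and a faster patient moves down.

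The CTT is one of only two cognitive instruments in the trial. The Background section reports that in the earlier phase 3 trial of hippocampal avoidance the cognitive difference was clearest on TMT Part B at 4 months and HVLT-R at 6 months, so the CTT stands in for one of the two measures that mattered there. The trial's hypothesis includes maintained cognitive function. If the boost arm slowed more, the literal rule could show fewer CTT deteriorations in that arm, and harm would read as preservation.

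**Working it through.** **1. The plan's own design figure.** The cognitive rule has no sample size, power or event rate of its own. The one design figure that can be recomputed is for the primary endpoint: "we will need 60 subjects (30 per arm) to detect a hazard ratio of 0.27".

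- Control rate in the experimental arm: 0.5^0.27 = 0.829, matching the stated 83%.
- Events (Schoenfeld, two-sided 5%, 80% power): (1.960 + 0.842)² ÷ (0.25 × (ln 0.27)²) = 18.3, so 19.
- Mean 6-month event probability: (0.500 + 0.171) ÷ 2 = 0.335.
- Subjects: 19 ÷ 0.335 = 56.7, or 58 in equal arms, close to the stated 60.
- Inflation: 60 ÷ (1 − 0.40) = 100, as stated.

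The figure reproduces, and nothing below changes it.

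**2. What the rule does algebraically.** If the same norms apply at both visits, the norm mean cancels:

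change in z = (follow-up − baseline) ÷ norm SD.

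Read numerically, the rule flags a patient when this change is −1 or lower. For completion time, that means a speed-up of at least one norm SD.

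**3. Worked patients.** Assumed values, not from the article: CTT in seconds, norm mean 50, norm SD 20, baseline 60 s, so z = (60 − 50) ÷ 20 = +0.5.

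| Follow-up | z at follow-up | Change in z | Literal rule | Sign reversed |
|---|---|---|---|---|
| 40 s (faster) | −0.5 | −1.0 | deteriorated | not deteriorated |
| 60 s (same) | +0.5 | 0 | not deteriorated | not deteriorated |
| 80 s (slower) | +1.5 | +1.0 | not deteriorated | deteriorated |

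**4. Size under assumed shifts.** Let the change in z be normal with mean μ (positive means slowing) and SD s. The article gives no values for either, so a range is shown. Truly slowed by at least 1 SD: 1 − Φ((1 − μ) ÷ s). Flagged by the literal rule: Φ((−1 − μ) ÷ s).

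| μ | s = 1.0: truly slowed | s = 1.0: flagged | s = 0.7: truly slowed | s = 0.7: flagged |
|---|---|---|---|---|
| 0 | 15.9% | 15.9% | 7.7% | 7.7% |
| 0.3 | 24.2% | 9.7% | 15.9% | 3.2% |
| 0.5 | 30.9% | 6.7% | 23.8% | 1.6% |
| 1.0 | 50.0% | 2.3% | 50.0% | 0.2% |

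Even where the two rates agree (μ = 0), they describe opposite tails and so different patients.

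**5. The arm comparison.** Suppose one arm has μ = 0 and the other μ = 0.5, both with s = 1.0. The true difference in deterioration is 30.9 − 15.9 = +15.0 percentage points. The literal rule shows 6.7 − 15.9 = −9.2 points. The sign flips because the arms differ by a shift. If they differed only in spread (μ = 0, s = 0.7 against 1.0), both columns would go from 7.7% to 15.9% and the direction would not flip.

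**The case against.** The strongest reply is that the inversion needs two premises the article does not state. First, the CTT must enter as raw time. If it enters as a norm-based score where higher is better, the rule works. Second, *decline* must mean a numerically lower value. The sentence defines deterioration, and the Background section uses *decline* for loss of function and of recall. If the word means worse performance, the rule is right for both tests. A reader might infer that the plan definitely counts faster patients as deteriorated; the document does not support that as a flat statement.

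This makes the point conditional but does not remove it. The formula subtracts a norm mean from the patient's value and divides by the norm SD, a step that a score already expressed against norms would not need. The rule speaks of a decline in score directly after that score has been defined numerically. The same paragraph uses *decrease* for FACT-BR and *decline* for the Barthel index, where both are numerical falls. The literal reading is therefore the more natural one.

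It can also be said that scoring direction belongs in an analysis plan or scoring manual. That would answer an omission. Here the formula and threshold are written out, and an analysis plan that copied them would carry the problem forward.

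Three further inferences do not hold:

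- **A composite that mixes decliners and improvers.** The article defines no composite of HVLT-R and CTT.
- **Wrong change-score tests.** The two-sided t-test and the regression give the same p-value whichever way the score is signed. Only the reading of the estimate is affected.
- **A Fisher test that is simply reversed.** Counting improvers tests a different event. A reversed result follows only under a shift model such as the one assumed above.

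The sensitivity analysis counts death and non-completion as deterioration, which is the intended direction under any reading. Under the literal rule, though, it would pool those patients with patients who got faster.

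**Conclusion.** The point holds in conditional form. The article fixes one unsigned formula and one decline rule for both tests. If the CTT is analysed as completion time and the rule is applied as it reads, a speed-up of at least 1 SD is counted as cognitive deterioration and a slowing of at least 1 SD is missed.

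The misclassification is complete in kind, since every patient flagged on the CTT would be an improver. How far the rates differ depends on shifts for which the article gives no figures, so the tabulated percentages are illustrations and not predictions.

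The reach is limited to the CTT part of an optional secondary endpoint. HVLT-R is unaffected if it is scored so that more recall is higher. The primary endpoint, the sample size and the significance level are untouched. Moderate severity is right. An analyst may well notice the direction, but settling it after outcome data by arm have been seen would be a post hoc choice.

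**What to change.** State the CTT metric, and fix the direction of deterioration separately for each test. If the metric is completion time, do one of the following:

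- Standardise the CTT as (norm mean − patient time) ÷ norm SD, so that lower is worse for both tests, and keep the 1-SD decline rule.
- Keep the present formula and define CTT deterioration as an increase of at least 1 SD in completion time from baseline.

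Use the same direction when reporting CTT change from baseline, so that the sign of the estimate is read correctly. If the CTT is instead entered as a norm-based score where higher is better, say so; no reversal is then needed.

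The cost is a sentence or two in the analysis plan, written before outcome data are compared by arm. Data collection, sample size and the choice of tests do not change.
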